# Tuberculosis screening improves preventive therapy uptake (TB SCRIPT) trial among people living with HIV in Uganda: a study protocol of an individual randomized controlled trial

**DOI:** 10.1186/s13063-022-06371-0

**Published:** 2022-05-12

**Keywords:** Tuberculosis, HIV, Screening, C-reactive protein, Tuberculosis preventive therapy, Randomized controlled trial

## Abstract

**Background:**

People living with HIV (PLHIV) have an increased risk of developing active tuberculosis (TB). To reduce the burden of TB among PLHIV, the World Health Organization (WHO) recommends systematic TB screening followed by (1) confirmatory TB testing for all who screen positive and (2) TB preventive therapy (TPT) for all TPT-eligible PLHIV who screen negative. Symptom-based screening remains the standard of care in most high TB burden settings, including Uganda. Despite having high sensitivity for active TB among antiretroviral-naïve PLHIV, symptom screening has poor specificity; as such, many high-risk PLHIV without active TB are not referred for TPT. C-reactive protein (CRP) is a promising alternative strategy for TB screening that has comparable sensitivity and higher specificity than symptom screening, and was endorsed by WHO in 2021. However, the impact of CRP-based TB screening on TB burden for PLHIV remains unclear.

**Methods:**

TB SCRIPT (TB Screening Improves Preventive Therapy Uptake) is a phase 3, multi-center, single-blinded, individual (1:1) randomized controlled trial evaluating the effectiveness of CRP-based TB screening on clinical outcomes of PLHIV. The trial aims to compare the effectiveness of a TB screening strategy based on CRP levels using a point-of-care (POC) assay on 2-year TB incidence and all-cause mortality (composite primary trial endpoint) and prevalent TB case detection and uptake of TPT (intermediate outcomes), relative to symptom-based TB screening (current practice).

**Discussion:**

This study will be critical to improving selection of eligible PLHIV for TPT and helping guide the scale-up and integration of TB screening and TPT activities. This work will enable the field to improve TB screening by removing barriers to TPT initiation among eligible PLHIV, and provide randomized evidence to inform and strengthen WHO guidelines.

**Trial registration:**

ClinicalTrials.gov NCT04557176. Registered on September 21, 2020.

**Supplementary Information:**

The online version contains supplementary material available at 10.1186/s13063-022-06371-0.

## Introduction

### Background and rationale

Tuberculosis (TB) remains the leading killer of people living with HIV (PLHIV) globally, accounting for one-third of all HIV-related deaths [1]. TB preventive therapy (TPT) is highly effective for PLHIV, reducing incident TB by 30–60% [2–7]. When combined with antiretroviral therapy (ART), TPT reduces all-cause mortality by as much as 40% relative to ART alone [3, 6]. Because of the proven benefit of TPT, the World Health Organization (WHO) has declared TPT an essential intervention for all PLHIV without active TB, regardless of latent TB infection (LTBI) status [8, 9]. To support the uptake of TPT among PLHIV, in 2011, the WHO endorsed a 4-part symptom screen (presence of cough, fever, night sweats, and/or weight loss) with high sensitivity and negative predictive value (NPV) to rule out active TB and thus enable the safe initiation of TPT for those who screen-negative [10]. However, this symptom screen has poor specificity among PLHIV, with meta-analyses demonstrating that 50–90% of all PLHIV initiating ART will screen positive for at least one symptom [11–14]. This poses a major barrier to prompt initiation of TPT, as symptom screening alone would require confirmatory testing in half or more of all PLHIV before TPT could be initiated. As such, a higher-specificity screening test to rule out active TB would help facilitate improved TPT initiation for PLHIV.

C-reactive protein (CRP) is a non-specific inflammatory marker whose levels rise in response to infection, including active TB. Prospective studies among individuals with advanced HIV initiating ART have shown CRP to meet the minimum thresholds for sensitivity (≥90%) and specificity (≥70%) established by WHO for an effective TB screening test [15–22], suggesting that CRP could be used to substantially increase TPT uptake among PLHIV and reduce the need for more costly confirmatory testing. Furthermore, CRP can be measured using a low-cost ($2 per test), rapid (results in 3 min), and simple (measured from capillary blood) point-of-care (POC) assay that can be easily implemented in low-resource settings. In response to multiple studies, including an individual patient data meta-analysis, demonstrating its comparable sensitivity and significantly higher specificity compared with symptom screening [15–17, 19, 20, 22], in 2021, the WHO recommended CRP for TB screening in PLHIV [23]. However, CRP is not widely used for TB screening globally, and the impact of CRP-based TB screening on TB case detection, TPT uptake, and TB burden among PLHIV remains unknown.

Here we describe the protocol of TB Screening Improves Preventive Therapy Uptake (TB SCRIPT), a randomized controlled trial conducted in three health centers in Uganda, which was designed to determine if TB screening based on POC CRP concentration improves clinical outcomes (reduced TB incidence and mortality) among outpatients with advanced HIV initiating ART through improved TPT uptake and detection of prevalent TB cases. This work will be critical to both improving selection of eligible PLHIV for TPT and helping guide the scale-up and integration of TB screening and TPT activities in TB-endemic countries.

### Objectives

The primary objective of TB SCRIPT is to compare the impact of POC CRP-based with symptom-based TB screening on 2-year TB disease outcomes. We will randomize participants to either POC CRP-based (intervention) or standard-of-practice symptom-based TB screening (control). All participants who screen positive will undergo confirmatory TB testing, while only participants who screen negative will initiate 12 weekly doses of isoniazid and rifapentine (3HP), a short-course TPT regimen. We will follow all eligible participants for 2 years to assess TB incidence and all-cause mortality. At the final study visit, we will collect sputum to ascertain active TB status from participants who have not been diagnosed with or treated for active TB during follow-up. The primary hypothesis for this objective is that participants randomized to POC CRP-based TB screening will have lower combined 2-year TB incidence and mortality (composite primary trial outcome), relative to participants randomized to symptom-based screening. The second objective is to compare the impact of POC CRP-based with symptom-based TB screening on (1) TPT uptake and (2) prevalent TB case detection, intermediate outcomes on the pathway to the combined primary trial outcome. The primary hypothesis for this objective is that participants randomized to POC CRP-based TB screening will have higher rates of TPT uptake and completion, determined via objective monitoring, and similar rates of prevalent TB case detection relative to participants randomized to symptom-based screening.

### Trial design and study setting

The TB SCRIPT trial is a phase 3, single-blinded, multi-center, randomized superiority trial evaluating the clinical impact of POC CRP-based TB screening on immediate and longer-term outcomes of PLHIV in Uganda. Uganda is among the world’s 30 high HIV/TB burden countries with an HIV prevalence of 6.2% and an annual TB incidence of 253 cases per 100,000 [1, 24]; among all TB cases, HIV prevalence is estimated at 45% [25]. Data from the 2014–2015 national TB prevalence survey estimate that half of all TB cases go undiagnosed each year, and the overall TB burden is greatest in urban areas [24].

We will randomize 1720 PLHIV presenting for routine ART initiation in three clinics (two public and one non-government/non-profit) in Kampala, Uganda, to either POC CRP-based TB screening (intervention) or symptom-based TB screening (control) with a 1:1 allocation ratio over a 2-year period. After randomization, we will perform baseline TB screening in accordance with the participant’s assigned TB screening strategy. Based on the results of baseline TB screening, we will either collect clinical specimens (urine, sputum) for confirmatory TB testing (urine lipoarabinomannan [LAM], sputum Xpert Ultra MTB/RIF, if screen-positive) or assess 3HP eligibility (if screen-negative, Fig. 1). Supported by study staff, clinic staff will provide all further care and follow-up for HIV, 3HP, and/or active TB, per routine clinic protocols. We will subsequently extract relevant clinical and outcome data from the clinic medical record at regular intervals (months 3, 6, 12, 18, and 24) for 2 years and collect sputum specimens for comprehensive TB testing (sputum Xpert Ultra, culture and drug susceptibility testing [DST]) at the final (24 months) study visit to ascertain 2-year active TB status.

**Fig. 1 Fig1:**
[figure not shown]
Study enrollment and baseline TB screening. Legend: (+) test-positive; (-) test-negative. Urine LAM-positive participants with risk factors for drug-resistant TB (prior TB treatment, contact with drug-resistant TB case) will undergo sputum Xpert Ultra testing for rapid detection of rifampin-resistance. All participants who test positive for TB (including urine LAM-positive/sputum Xpert Ultra-negative participants) will be referred to routine clinicians for TB treatment initiation

## Methods

### Eligibility criteria

We will screen ART-naïve PLHIV presenting for routine outpatient HIV care for study eligibility. We will enroll adults (age ≥ 18 years) with a confirmed HIV-positive test result and CD4 count ≤350 cells/μL and capacity to provide written (or witnessed verbal, if illiterate) informed consent. We will exclude those who have completed treatment for active pulmonary or extra-pulmonary TB within the past 2 years; completed a full course of any approved TPT regimen within the past year; are actively taking any internationally approved medication for TB treatment (e.g., fluoroquinolones) for any reason, within 2 weeks of study entry; have a prior history of combined ART for HIV treatment for any duration; or who currently reside 25 km outside the enrollment site, have plans to move 25 km outside their enrollment site in the next 2 years, or plan to transfer their HIV care from the enrollment site.

### Informed consent

The study team will obtain written informed consent in English or the local dialect (Luganda). For participants who cannot read or write, we will obtain verbal consent and obtain a thumbprint, and a witness will sign the informed consent document. We will obtain separate written informed consent for collection and storage of biological specimens.

### Interventions

We will compare the effectiveness of two WHO-approved TB screening strategies for PLHIV: POC CRP (intervention) and the WHO 4-part symptom screen (control).

#### Intervention arm: POC CRP-based TB screening

For participants randomized to POC CRP-based TB screening, we will record POC CRP concentrations measured from capillary blood obtained via finger prick using a standard sensitivity POC assay (iCHROMA CRP assay; BodiTech, South Korea). The iCHROMA CRP assay is a US Food and Drug Administration (FDA)-approved, fully quantitative, lateral flow-based fluorescence sandwich immunoassay with a detection range of 2.5–300 mg/L and excellent stability after more than 18 months of storage under the recommended conditions.

Although the recent WHO TB screening guidelines recommend using a cut-point of 5 mg/L to maximize sensitivity of CRP for active TB, we selected a cut-point of 8 mg/L prior to the updated WHO recommendations based on our own previously published research demonstrating a CRP cut-point of 8 mg/L to have 90% sensitivity and 70% specificity for culture-confirmed TB [20, 26, 27]. Participants with POC CRP levels ≥8 mg/L will be classified as screen-positive while those with POC CRP levels < 8 mg/L will be classified as screen-negative.

#### Control arm: symptom-based TB screening

For participants randomized to symptom-based TB screening, we will record the presence or absence of current cough, fever, night sweats, and weight loss in the past 30 days using a standardized script. In accordance with the current WHO and Ugandan TB screening guidelines, participants with ≥1 symptom will be classified as screen-positive and participants with none of the 4 symptoms will be classified as screen-negative [8].

#### Both arms

In both arms, we will use the results of baseline TB screening to guide decisions regarding 3HP initiation and confirmatory TB testing (Fig. 1).

##### Screen-negative participants

We will offer 3HP to all screen-negative participants (POC CRP < 8 mg/L in the intervention arm; absence of all 4 symptoms in the control arm) meeting local 3HP eligibility criteria. 3HP will be initiated no earlier than 2 weeks after ART initiation. Participants initiating 3HP will be managed in accordance with local guidelines and instructed to bring 3HP bottles at every visit during the period of 3HP prescription.

##### Screen-positive participants

We will collect spontaneously voided urine and spot sputum specimens (induced, if necessary) from all screen-positive participants (POC CRP ≥8 mg/L in the intervention arm; presence of ≥1 symptom in the control arm) for urine LAM (Alere Determine TB-LAM) and sputum Xpert Ultra testing. In accordance with current WHO guidelines, sputum Xpert Ultra testing will be performed if (1) urine LAM is negative or (2) urine LAM is positive and the participant has risk factors for drug-resistant TB (prior TB treatment, contact with drug-resistant TB case). Participants who test positive for TB by urine LAM and/or sputum Xpert Ultra will be referred to clinicians for TB treatment initiation. To maximize real-world relevance, sputum will not be submitted for mycobacterial culture because most HIV programs in high burden countries use Xpert (standard cartridge or Ultra) as the confirmatory test for TB. Participants who screen-positive but test negative by urine LAM and sputum Xpert Ultra will not be given 3HP at the time of enrollment (as their risk of active TB remains non-negligible), but will be eligible for TPT initiation at the discretion of treating (non-study) clinicians throughout the follow-up period.

### Participant timeline

After baseline study procedures, routine clinic staff will provide all further care and follow-up for HIV, TPT, and/or active TB treatment. Routine clinical care for all patients initiated on ART includes blood draw for pre-ART labs, HIV viral load at 6 months and as appropriate thereafter, and clinic visits at weeks 2 and 6 and then months 3, 6, 12, 18, and 24 post-ART initiation. Patients initiated on 3HP or TB treatment have additional visits for active TB screening, medication adverse event (AE) monitoring, adherence assessments, and refills, per routine clinic protocols. To capture clinical and outcome data for this trial, we will conduct brief follow-up interviews and extract relevant data from the clinic medical record at regular intervals for 2 years (months 3, 6, 12, 18, and 24). At the final (24-month) study visit, we will collect sputum specimens from all participants who have not been treated for TB during the study for the final active TB assessment. Table 1 describes the schedule of study activities performed by study staff and the schedule of clinic activities performed by routine clinic staff for PLHIV initiating ART.

**Table 1 Tab1:** Schedule of study activities

Timepoint	Entry	Weeks				Months						
	0	2	4	6	8	3	4	5	6	12	18	24
**Enrollment**												
Eligibility screen	•											
Informed consent	•											
Randomization	•											
**Study activities**												
Baseline TB screening by trial arm	•											
Urine pregnancy testing	•											
Capillary blood β-hCG testing	•											
Banking of serum/plasma and urine	•					•			•	•	•	•
***Screen-negatives***												
TPT eligibility assessment	•											
Liver enzyme testing (if eligible for TPT)	•											
TPT initiation		•										
TPT adherence monitoring				•		•						
***Screen-positives***												
Urine LAM	•											
Xpert Ultra (if LAM-negative or at risk for DR TB)	•											
TB treatment initiation		•										
TB treatment adherence monitoring						•			•			
***Final TB status assessment***												
Xpert Ultra												•
Liquid mycobacterial culture												•
Drug susceptibility testing												•
**Routine clinic activities**												
CD4 count	•											
Blood chemistry	•											
Complete blood count	•											
ART initiation	•											
Routine clinic follow-up visit		•		•		•			•	•	•	•
HIV viral load									•	•	•	•
***Participants initiated on anti-TB therapy***												
AE monitoring		•	•		•	•	•	•	•			
TB treatment adherence monitoring		•	•		•	•	•	•	•			
Medication refills		•	•		•	•	•	•	•			

### Risks to study participants

As this trial is comparing two WHO-endorsed TB screening strategies, the risk of study participation is no greater than routine care. People with prevalent TB may be missed by screening and/or inadvertently initiated on TPT; prevalent TB cases initiated on 3HP are at increased potential risk for developing acquired drug resistance. Missed prevalent TB cases, including all drug-resistant TB cases, will be managed by routine clinicians in accordance with local guidelines. Conversely, PLHIV without active TB may have a false-positive screen and miss the opportunity to receive study-initiated 3HP. The risk of injury to study participants is minimal. In the unlikely event of injury as a result of study participation, standard treatments will be made immediately available at the clinic site and/or Mulago National Referral Hospital; no other form of compensation for injury will be provided.

### Participant retention

To promote retention for participants in both trial arms, we will record participants’ phone numbers and home address at study entry and review/update their contact information at every study visit (with participants’ consent). We will provide phone call reminders of upcoming clinic appointments and reimbursement for transportation expenses for all scheduled study visits.

### Outcomes

The primary trial endpoint is a composite outcome of microbiologically confirmed incident TB and all-cause mortality, measured as time to first diagnosis of incident TB or death from any cause. Microbiologically confirmed incident TB is defined as active TB diagnosed by either culture, one non-trace positive Xpert Ultra result or two trace-positive Xpert Ultra results, or positive urine LAM result from 3 months after randomization to the end of follow-up (at 2 years, or at the time of last contact for participants who are lost to follow-up). To assess active TB status at the end of follow-up, 2 spot sputum specimens will be collected from all participants who have not taken anti-TB treatment during the study at the final (24 months) study visit for sputum Xpert Ultra testing, liquid culture, and drug susceptibility testing (for participants who received any TPT). Secondary outcomes are presented in Table 2.

**Table 2 Tab2:** Secondary outcomes of the TB SCRIPT trial

Outcome	Numerator	Denominator

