**A. TB incidence**		
Number diagnosed with microbiologically confirmed incident TB within 2 years	# diagnosed with incident TB (incident TB = positive non-trace Xpert Ultra result, two trace Xpert Ultra results, or ≥ 1 positive culture result > 3 months after study entry)	None
2-year incidence of microbiologically confirmed TB	# diagnosed with incident TB	# randomized to corresponding study arm - # treated for prevalent TB (prevalent TB = active TB diagnosed ≤3 months of study entry)
Time to microbiologically confirmed incident TB diagnosis	Days from 3 months post-enrollment to incident TB diagnosis (or censoring)	
Incident rate of microbiologically confirmed TB	# diagnosed with incident TB	(# randomized to corresponding study arm - # treated for prevalent TB)/time in person-years
Number diagnosed with drug-resistant incident TB within 2 years	# diagnosed with incident drug-resistant TB (drug-resistant TB = DST-detected resistance to drugs administered for TPT [e.g., isoniazid])	None
2-year incidence of drug-resistant TB among people receiving TPT	# diagnosed with incident drug-resistant TB	# received TPT of any duration

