**D. Prevalent TB diagnosis**		
Number microbiologically confirmed prevalent TB cases detected by the screening test	# screen-positives diagnosed with prevalent TB (diagnosed = a positive urine LAM result, one non-trace positive or two trace-positive Xpert Ultra results ≤3 months of study entry)	
Proportion microbiologically confirmed prevalent TB cases detected by the screening test	# screen-positives diagnosed with prevalent TB	# randomized to corresponding study arm
Number microbiologically confirmed prevalent TB cases missed by the screening test	# screen-negatives diagnosed with prevalent TB	None
Proportion microbiologically confirmed prevalent TB cases missed by the screening test	# screen-negatives diagnosed with prevalent TB	# randomized to corresponding study arm
Number diagnosed with microbiologically confirmed prevalent TB	# screen-positives diagnosed with prevalent TB + # screen-negatives diagnosed with prevalent TB	None
Microbiologically confirmed TB prevalence	# screen-positives diagnosed with prevalent TB + # screen-negatives diagnosed with prevalent TB	# randomized to corresponding study arm

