#### Final TB status assessment

For all participants who have not taken anti-TB treatment during follow-up, we will collect 2 spot sputum specimens at the final (24 months) study visit for sputum Xpert Ultra testing; repeat Xpert Ultra testing, if the initial test is trace-positive; and liquid culture and drug susceptibility testing (DST). Speciation testing will be performed on all positive cultures to confirm the presence of *M. tuberculosis* complex using Ziehl-Neelsen smear microscopy for detection of acid-fast bacilli and SD MPT64 (Standard Diagnostics Bioline TB Ag MPT64, South Korea) for rapid *M. tuberculosis* antigen detection. DST will include susceptibility testing to all first-line TB medications including isoniazid and rifamycin-based drugs. Participants will be classified as having incident TB if at least one of the following criteria are met: at least one sputum culture positive for *M. tuberculosis* complex, one non-trace-positive Xpert Ultra result, or two trace-positive Xpert Ultra results.

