### Statistical methods

#### Primary and secondary outcomes

The primary trial outcome is a 2-year composite endpoint of microbiologically confirmed incident TB and all-cause mortality, measured as time to first diagnosis of incident TB or death from any cause. The primary analysis will be by intention-to-treat (ITT), including all participants randomized without regard to the results of baseline TB screening, and we will use a two-sided alpha (0.05 significance) in assessing the effect of the intervention on the primary outcome. Participants with prevalent TB will be included in the analysis to preserve the randomized groups (the ITT principle) but excluded from the outcome of incident TB because subsequent disease is more likely to represent relapse or failure (and these participants will not routinely receive TPT). Time from randomization to first event (diagnosis of incident TB or death from any cause) will be analyzed using the log rank test and Cox proportional hazards models, adjusted for the study site. If data are missing or a patient is lost to follow-up, a patient’s data will be censored in the analysis at the date of last known contact. We will also use the Mantel-Haenszel method to determine standardized incidence rates and incidence rate differences. Balance at baseline on all known and suspected prognostic factors will be assessed, and if important imbalances are found (e.g., differences in median baseline CD4 count), a sensitivity analysis will be conducted using a Cox model to adjust for these factors. We will also assess the impact of clinician-initiated co-interventions (e.g., clinician-initiated TPT, clinician-initiated TB treatment) on the primary outcome. We will conduct a sensitivity analysis in which these participants are censored as soon as they are initiated on TPT or TB treatment by non-study clinicians. Standard checks for variation by enrollment site will also be planned. Secondary outcomes for the primary objective include the individual primary endpoints (TB incidence and mortality analyzed separately) and 2-year isoniazid-resistant TB incidence and will be analyzed using a similar approach; there will be no adjustment for multiplicity since these are pre-specified secondary outcomes.

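### Microbiologically confirmed incident TB includes urine LAM in the primary composite but not in the Table 2 outcomes meant to be its TB component, and the 3-month boundary is assigned two ways

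*Protocol article*

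**What the plan says.** The Outcomes section states the TB part of the primary composite: "Microbiologically confirmed incident TB is defined as active TB diagnosed by either culture, one non-trace positive Xpert Ultra result or two trace-positive Xpert Ultra results", continuing "or positive urine LAM result from 3 months after randomization to the end of follow-up".

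Table 2, part A, gives its own definition under the same name for the secondary outcomes: "incident TB = positive non-trace Xpert Ultra result, two trace Xpert Ultra results, or ≥ 1 positive culture result > 3 months after study entry". Urine LAM is not on that list.

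Table 2, part D, does name LAM when it defines prevalent TB: "diagnosed = a positive urine LAM result, one non-trace positive or two trace-positive Xpert Ultra results ≤3 months of study entry".

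The Statistical methods (Primary and secondary outcomes) tie the two levels together: "Secondary outcomes for the primary objective include the individual primary endpoints (TB incidence and mortality analyzed separately". The Table 2A outcomes are thus presented as the TB half of the primary endpoint.

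**The concern.** One term has two case definitions. If TB incidence is the component of the composite, a reader expects every TB event in the composite to be a TB case in the component. As written, LAM-only cases break that rule.

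The omission is hard to read as shorthand, because part D of the same table names LAM where it is meant to count. A programmer working from Table 2 would reasonably take its absence from part A as deliberate.

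At stake is the reading of the composite through its components. The TB-incidence results could leave out cases that contributed to the primary result. If the conflict is settled only after outcomes are known, the choice of definition could depend on the data.

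**Working it through.** **Definitions side by side**

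| Place | Use | Urine LAM | Culture | Xpert Ultra | Timing |
|---|---|---|---|---|---|
| Outcomes | incident TB, primary | counts | counts, species not named | one non-trace or two trace | from 3 months |
| Table 2A | incident TB, secondary | not listed | at least one, species not named | one non-trace or two trace | after 3 months |
| Final TB status assessment | incident TB at month 24 | not listed (sputum only) | *M. tuberculosis* complex | one non-trace or two trace | month-24 visit |
| Table 2D | prevalent TB | counts | not listed | one non-trace or two trace | up to and including 3 months |

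The Outcomes and Table 2A rows differ in two cells: LAM and the treatment of the 3-month point.

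**Case 1: positive urine LAM at month 4, no other positive test, treated.**
1. Outcomes: a primary event.
2. Table 2A: not incident TB, because LAM is not listed.
3. Table 2D: not prevalent TB, because it falls after 3 months. The same result at month 2 would have been prevalent TB.
4. Month 24: Outcomes and Final TB status assessment collect sputum only from participants who have not taken anti-TB treatment, so the protocol schedules no later test that could add the case to Table 2A.

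Table 1 lists urine LAM at entry only. A case like this needs a clinician-ordered test, which the Blinding section allows at any time.

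**Case 2: non-trace Xpert Ultra dated exactly at 3 months.** Outcomes makes it incident. Table 2, parts A and D, makes it prevalent. The Statistical methods remove participants with prevalent TB from the incident-TB outcome, so the same diagnosis is an event under one section and excluded under another.

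**The plan's own figures.** Inputs from Sample size: 860 per arm, 12% loss, 12.5% in the control arm, 35% relative reduction, two-sided alpha 0.05.
- Evaluable per arm: 860 × 0.88 = 756.8.
- Events: 756.8 × 0.125 = 94.6 and 94.6 × 0.65 = 61.5 (stated: 95 and 62).
- Power, pooled variance, with p1 = 0.125, p2 = 0.08125 and mean 0.103125: z = [0.04375 × √756.8 − 1.96 × √(2 × 0.103125 × 0.896875)] / √(0.109375 + 0.074648) = (1.2036 − 0.8430) / 0.4290 = 0.84, which gives 0.80 (stated: 80%).

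The stated power reproduces.

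**How many cases could differ.** The document gives no LAM-only share, so only a scale can be shown. Assume that the planned 7.3% TB incidence includes LAM-only cases and that the 35% reduction applies to TB. Expected TB cases are then 756.8 × 0.073 = 55.25 in control and 55.25 × 0.65 = 35.91 in intervention, 91.16 in total. For an assumed LAM-only share f, the discordant cases number 91.16 × f:
- 0%: 0
- 5%: 4.6
- 10%: 9.1
- 20%: 18.2
- 30%: 27.3

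These figures follow the chosen share and are not estimates for this trial.

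**The case against.** The strongest reply is that the primary endpoint is not ambiguous on LAM. Outcomes defines it explicitly, and Table 2 is headed as secondary outcomes. With no LAM scheduled after entry, LAM-only incident cases could be close to none. All of this stands, and it limits the weight of the point. It does not remove the conflict between the two definitions.

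Four stronger readings are tempting, and the document does not support them.

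- **Loss of power.** Under the assumptions above, with 5% to 30% LAM-only, a composite built on the Table 2A list would have a control rate of 12.1% to 10.3% and power of 0.79 to 0.71. That requires an analyst to discard the explicit primary definition, as well as shares the document does not give. Nor does Sample size say whether the 7.3% includes LAM-only cases.
- **False TB cases from other mycobacteria.** A reader might infer that Table 2A, by accepting any positive culture, counts cases that the primary endpoint rejects. Outcomes also accepts culture without naming a species, so culture does not separate the two. Final TB status assessment covers the question: "Speciation testing will be performed on all positive cultures to confirm the presence of" *M. tuberculosis* complex, and its classification requires "at least one sputum culture positive for *M. tuberculosis* complex, one non-trace-positive Xpert Ultra result, or two trace-positive Xpert Ultra results".
- **Components that should sum to the composite.** They would not sum even with identical TB definitions. The composite runs from randomization in everyone randomized. Table 2A starts its time-to-diagnosis clock at 3 months and removes those treated for prevalent TB from its denominators. A participant with TB who later dies counts in both components.
- **A serious misclassification at month 3.** Month 3 is a scheduled visit with interview and record extraction, but Table 1 places no diagnostic TB test there. Only diagnoses dated exactly at 3 months are affected.

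**Conclusion.** The point holds as an inconsistency of definition. Urine LAM counts as confirmed incident TB in the primary composite and is absent from the explicit Table 2A definition of the same term, although the plan calls TB incidence an individual part of the primary endpoint. A treated LAM-only case after month 3 is a primary event and appears in Table 2 as neither incident nor prevalent TB. A diagnosis at exactly 3 months is classed in two ways.

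The size is unknown. It depends on how often clinicians order urine LAM during follow-up and how often it is the only positive test, and the document gives neither figure. It may be small. Nothing here shows an error in the primary definition or in the 80% power. The correction is worth making because it is cheap and is best settled before outcomes are known. It does not threaten the primary analysis.

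**What to change.** Replace the Table 2A wording with a reference to the Outcomes definition, written out once: culture positive for *M. tuberculosis* complex (as in Final TB status assessment), one non-trace or two trace-positive Xpert Ultra results, or a positive urine LAM.

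Use one boundary rule in Outcomes, Table 2 and the Statistical methods, for example up to and including 3 months as prevalent and later than 3 months as incident. That choice changes the Outcomes wording only for diagnoses dated exactly at 3 months.

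Optionally, report TB incidence without LAM-only cases as a sensitivity analysis, so that readers can see what the LAM criterion contributes.

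The cost is a wording edit and a little analysis work. No new data are needed.
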